***Parent measures***				

Parenting practices	Parent Behavior Checklist (nurturing, harsh discipline) [57] Over-involved/protective parenting [10,35]	Baseline 1 & 2 years	32 8	Secondary outcome (intervention mechanism for impacting on child).

Mental health	Depression, Anxiety, Stress Scale [58]	Baseline 1 & 2 years	21	Secondary outcome (impact on parent wellbeing).

Wellbeing	SF-12 [59]	Baseline	12	Secondary outcome (economics measure).
	Assessment of Quality of Life (AQoL-8D) [49]	1 & 2 years	35	Secondary outcome (economics measure).

***Intervention 'process' measures***				

Fidelity	Group sessions content checklists, rated by facilitator and researcher	6 month appraisal	6-8	Secondary outcome (integrity of intervention delivery). Adapted for this study.

Acceptability to parents	Perceptions of screening process Perceptions of group sessions content, group facilitator	6 month appraisal	4 15	Secondary outcome (implications for translation/dissemination uptake by families). Adapted for this study.

Cost-effectiveness	Child and adult health service use	1 & 2 years	6	Secondary outcome (for policy/decision makers considering translation/dissemination). Generated for this study.

After scoring, the study team will notify parents by letter if their child does not score highly on temperamental inhibition and is therefore ineligible for the trial. Eligible parents will be mailed the detailed trial Information Statement and Consent form with the baseline questionnaire ascertaining family risk for internalising problems and more detailed demographic characteristics (see Table 1). The study team will also telephone all eligible parents to explain trial procedures in detail and answer parents' questions.

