### Intervention

#### Content

For this population-level randomised trial, the *Cool Little Kids *parenting intervention consists of manualised parenting group sessions as previously tested in [name]'s efficacy research [41]. Parents will receive a 'workbook' at the first parenting session that presents information on the nature of inhibition, fears, anxiety and emotional distress, and the developmental trajectory of internalising problems. Thereafter, it details instructions in exposing children to their specific triggers for emotional distress to develop reality-testing and coping skills. In addition, it presents effective ways of parenting inhibited children, and methods for parents to manage their own worries and distress. The latter component involves parents applying strategies for children to themselves, plus a section on cognitive restructuring. Parents are taught how to think more realistically to manage their own concerns, so that they can gradually introduce cognitive techniques to their children as they grow older. The manual is supplemented with extensive examples and detailed exercises. It also contains information on adult mental health problems and encourages parents to seek professional help if relevant. Families with low literacy, and culturally and linguistically diverse families, will be supported by using plain English content.

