#### Process - Control group

Families in the control arm will receive usual teaching and care from their preschool, early childhood and health services in the community. This may include advice on children's behaviour, but would not include a structured, evidence-based parenting program for temperamental inhibition or internalising problems.

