### Outcome measurement

Approximately one (2012) and two (2013) years after baseline, a clinician blind to group allocation will interview parents to ascertain child internalising diagnoses (see Table 1). These interviews will be conducted by telephone, which has demonstrated validity and is less expensive than face-to-face interviews [48]. A questionnaire mailed to parents will further measure child internalising symptoms, parenting practices, parent mental health and service use.

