### Data analyses

Regression analyses will compare child outcomes and costs at school-entry (1 and 2 years after baseline) between the intervention and control arms using the intention-to-treat principle, where participants are analysed in the groups to which they were randomised. Logistic regression will be used for binary outcomes (presenting the percentages for each trial arm and odds ratio between them) and linear regression for continuous outcomes (presenting the mean and standard deviation for each trial arm and mean difference between them). Both unadjusted analyses and analyses adjusted for potential confounding factors determined *a priori *before randomisation (child gender, family socioeconomic level, parent mental health) will be implemented. Tests of interaction, specified *a priori*, will explore differential intervention effects for children who are higher on risk factors at baseline. In line with [name]'s second efficacy trial [40], we anticipate larger group differences might emerge for children who are higher on risk factors at baseline.

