The underlying principle in identifying costs relevant to the economic evaluation is that the inclusion/exclusion criteria should mirror the study perspective. This economic evaluation intends to adopt a largely societal perspective, so all costs to the health sector, participants and their families as well as other sectors impacted upon by the intervention will be included. As there are no previous economic evaluations in this area, a comprehensive resource use questionnaire is proposed to capture a wide variety of resource use for both parents and children (including time costs of parents). Costs associated with the initial research, design and set-up of the intervention and the development of any program materials will be excluded, as these are largely one-off 'sunk' costs (unrecoverable past expenditures), and will not be incurred in on-going routine implementation of the intervention.

The technique of 'bootstrapping' will be used to obtain confidence intervals for cost effectiveness ratios, since parametric techniques are inappropriate for use on both skewed variables and ratios. The sensitivity of the results will also be tested against: different discounting scenario; variation in the utility weights for the children; and, differences in unit cost prices. Costs falling upon the health sector, patients or their families, the government and other sectors will be presented in total and disaggregated form.

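### Service use is scheduled only after randomisation, so cost comparisons cannot be adjusted for prior use: a loss of precision, not a bias

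*Protocol article*

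**What the plan says.** Table 1, in the cost-effectiveness row of the intervention process measures, lists "Child and adult health service use" as a six-item measure taken at 1 and 2 years. Outcome measurement places it in the follow-up mailing: "A questionnaire mailed to parents will further measure child internalising symptoms, parenting practices, parent mental health and service use". The Recruitment and participants section describes the form sent before consent as a "baseline questionnaire ascertaining family risk for internalising problems and more detailed demographic characteristics", with no mention of service use.

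Economic Evaluation states that "a comprehensive resource use questionnaire is proposed to capture a wide variety of resource use for both parents and children", and gives no time points for it.

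Under Data analyses, "Regression analyses will compare child outcomes and costs at school-entry (1 and 2 years after baseline) between the intervention and control arms", both unadjusted and adjusted for child gender, family socioeconomic level and parent mental health. Prior service use and prior cost are not among the covariates.

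For the control arm, the comparator is "usual teaching and care from their preschool, early childhood and health services in the community". The intervention workbook "encourages parents to seek professional help if relevant".

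**The concern.** Cost-effectiveness is aim (c) of the trial, and costs are compared between arms by regression. The Economic Evaluation section itself notes that such variables are skewed. In a skewed cost distribution a few heavy users can move a mean difference, and earlier use is the most direct predictor of later use. The selection criteria do not exclude families because the child or parent is already in treatment, and no measure shown identifies them at entry.

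Two things are at stake. First, the cost interval will be wider than it need be, and a chance imbalance in prior use cannot be corrected directly. Second, the report will not be able to state how many families in each arm were already receiving care at entry. An analysis plan written later cannot repair either one, because it can only use values collected before allocation.

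**Working it through.** **1. The schedule, read across the document.**

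| Place | Timing given |
|---|---|
| Table 1, service use | 1 and 2 years |
| Table 1, parenting practices; parent mental health (DASS) | Baseline, 1 and 2 years |
| Table 1, SF-12 | Baseline |
| Table 1, Strengths & Difficulties Questionnaire | Screening, 1 and 2 years |
| Table 1, developmental status (PEDS) | RCT baseline |
| Outcome measurement, service use | about 1 and 2 years after baseline |
| Economic Evaluation, resource-use questionnaire | none given |

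The table names a pre-allocation time point where one applies. The service-use row has none, and the text on outcome measurement agrees with it.

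**2. The plan's own figure.** The article gives no precision or power figure for costs. The sample size supplies the number analysed per arm, so it was checked first. Inputs from the Sample size section are 64% versus 50%, 80% power, 5% level and 20% loss. A two-sided test and 1:1 allocation are assumed.

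n per arm = [1.96 × √(2 × 0.57 × 0.43) + 0.8416 × √(0.64 × 0.36 + 0.50 × 0.50)]² / 0.14² = [1.372 + 0.583]² / 0.0196 ≈ 195.1, rounded up to 196.

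Total 392; 392 / 0.80 = 490, which agrees with around 500. The sample size is sound and does not depend on this point. With 500 recruited and 20% lost, 500 × 0.80 / 2 = 200 per arm are analysed.

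**3. Precision forgone.** Let r be the correlation between baseline and follow-up cost. The document does not give r, so a range is assumed. Linear adjustment multiplies the residual variance by 1 − r² and the interval width by √(1 − r²).

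| r (assumed) | Variance factor | Width factor | Interval narrower by |
|---|---|---|---|
| 0.3 | 0.91 | 0.954 | about 5% |
| 0.5 | 0.75 | 0.866 | about 13% |
| 0.6 | 0.64 | 0.800 | 20% |

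These are gains over no adjustment. The planned model already adjusts for parent mental health and socioeconomic level. To the extent that those carry information on prior use, the further gain is smaller.

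**4. Chance imbalance.** With 200 per arm, the standard error of the baseline difference is √(2/200) = 0.10 SD, so 95% of randomisations fall within 1.96 × 0.10 ≈ ±0.20 SD. An imbalance at that limit shifts the expected unadjusted cost difference by r × 0.196: 0.06 SD at r = 0.3 and 0.12 SD at r = 0.6. The unadjusted standard error of the cost difference is itself 0.10 SD. This is ordinary sampling error that the unadjusted interval already allows for. A baseline value would remove it.

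**The case against.** **Randomisation protects the comparison.** A reader might infer that a follow-up difference in service use mixes care already under way with care prompted by allocation, so that the two cannot be separated. The documents do not support this. Allocation is random, in blocks within each preschool, and analysis follows intention to treat. Prior care is therefore balanced in expectation, and the difference between arms estimates the effect of allocation. This objection stands in full.

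**Differing background care can still be seen.** A reader might also infer that the trial could not show whether the arms received unequal outside treatment. Service use is recorded in both arms at 1 and 2 years, which is the measurement that shows it. If the workbook leads parents to seek help, that is part of the effect and cost of the intervention. It belongs in the largely societal perspective that the plan adopts. This stands too.

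**Some baseline adjustment is possible.** Costs can be adjusted for the three named covariates, and SF-12 is also taken at baseline. What cannot be adjusted for is prior use or cost.

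**The article is condensed.** Table 1 is headed as covering measures used in analysing outcomes, and the demographic items have no row in it. The recall period of the six items is not given; a 12-month or since-baseline window would delimit use after allocation, though it would not identify families in treatment at entry. The broader resource-use questionnaire might be a separate instrument. This is why the point says only that no baseline record is shown. It does not remove the point, because the time points for service use are stated, in two places that agree.

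**The gain may be small.** The correlation is assumed, cost is a secondary outcome with no power claim, and time-efficient assessment is one of the trial's stated aims. This limits the weight of the point to that of a cheap improvement.

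**Conclusion.** The point holds in a limited form. As scheduled, the comparisons of cost and service use cannot be adjusted for pre-randomisation use or cost, and treatment status at entry cannot be reported by arm. There is no bias in the arm comparison and no effect on the primary outcomes or the sample size.

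The loss in interval width is at most about 5% to 20% relative to no adjustment. It is smaller beyond the covariates already planned. That range rests on an assumed correlation of 0.3 to 0.6 and on linear adjustment. It also rests on reading Table 1 and the Outcome measurement section as the complete schedule for service use. If the full protocol shows a baseline resource-use form, the point falls away apart from the need to align the two descriptions.

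**What to change.** 1. Add the six service-use items for child and parent to the baseline questionnaire already mailed to eligible families before randomisation. State the recall window and ask about current treatment.
2. Change the time points in the Table 1 service-use row to Baseline, 1 & 2 years.
3. In Data analyses, add the baseline value as a covariate in the adjusted cost and service-use comparisons, and report treatment status at entry by arm.
4. State whether the six-item measure in Table 1 and the comprehensive questionnaire in Economic Evaluation are the same instrument, and give the recall period and time points.

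The cost is six items plus a question on current treatment, on a form that is already sent, and one more covariate. The downside is a slightly longer baseline form. The change must be made before baseline collection closes, since the value cannot be recovered cleanly afterwards.

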### Selection criteria

#### Inclusion criteria

Parents will be eligible for the universal screening component of the study (completing the brief parent-report questionnaire) if their child is enrolled for their preschool year (i.e. the year prior to school) at a participating preschool/kindergarten service. They will be eligible to join the trial if the child scores ≥85^th ^percentile on the inhibition subscale of the Short Temperament Scales [47].

#### Exclusion criteria

Exclusion criteria are (1) parents with insufficient English to participate (determined by parent or teacher report, or by the study team following up on insufficiently completed screening questionnaires) and (2) children with major health or developmental problems who are considered unlikely to benefit from the intervention. Major health or developmental problems will be discussed on a case-by-case basis, which mirrors what would happen when subsequently translated to the broader population. As exclusion occurs before randomisation, it in no way affects the trial's internal validity.

### Allocation

After recruitment and consent, the statistician will coordinate a concealed web-based randomisation process. Computer-generated sequences of random numbers will be used to determine the trial arm status of each child. A block randomisation process, stratified for each preschool separately, will minimise the imbalance between the numbers of intervention and control participants within each preschool. After families are randomised, the study team will notify all parents by letter whether they are in the intervention or control arm, and arrange group session bookings for intervention parents. Participant allocation will be concealed to the clinician assessing diagnostic outcomes; however, the group facilitators and parents cannot be blinded to their group allocation.

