### Sample size

The randomised trial will have a sample size of around 500 inhibited children, providing 80% power at the 5% level of significance to detect the level of reduction in internalising problems found in [name]'s prior efficacy trials, namely a 14% reduction in child internalising disorders between the intervention (50%) and control (64%) groups [41]. This sample size estimation considers an achievable attrition rate for a quality trial, allowing for up to 20% loss to follow up.

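### Randomisation is blocked within each preschool, but neither planned model includes preschool; taken alone this makes standard errors slightly too large and costs a little power

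*Protocol article*

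**What the plan says.** Under Allocation, the unit of randomisation is the child: "Computer-generated sequences of random numbers will be used to determine the trial arm status of each child". The sequence is restricted by preschool: "A block randomisation process, stratified for each preschool separately, will minimise the imbalance between the numbers of intervention and control participants within each preschool". Block size is not given.

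Under Data analyses, the models for both types of outcome are named: "Logistic regression will be used for binary outcomes (presenting the percentages for each trial arm and odds ratio between them) and linear regression for continuous" ones. Two versions are planned, one unadjusted and one adjusted for factors fixed before randomisation, which are listed as "child gender, family socioeconomic level, parent mental health". Preschool is not on the list, and the article nowhere mentions a stratum term, a random effect, a conditional analysis or a clustered standard error.

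Under Sample size, about 500 children are planned, "providing 80% power at the 5% level of significance", for "a 14% reduction in child internalising disorders between the intervention (50%) and control (64%) groups", with up to 20% loss. Preschool plays no part in that calculation.

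**The concern.** Blocking within preschool shares each preschool's children almost equally between the arms. Differences between preschools then largely cancel out of the treatment comparison, so its true sampling variance is smaller than under simple randomisation. A model without preschool does not know this. It keeps the between-preschool variation in its error term and reports a standard error for a less efficient design than the one used.

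The consequence depends on the outcome type. For linear models of symptom scores, the interval is wider than it needs to be. For the logistic model of diagnosis, the loss is in power: accounting for preschool does not shrink the standard error of the log odds ratio, but it targets a conditional odds ratio that lies further from 1.

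Some preschool variation is plausible, since the Recruitment section says that the four areas are chosen to cover a range of sociodemographic circumstances.

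**Working it through.** **Inputs from the article.** Rates 50% and 64%; two arms; about 500 randomised; up to 20% lost, so about 400 analysed, 200 per arm; 5% level (taken as two-sided, because that reproduces the plan); 80% power.

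**Inputs assumed.** Preschool ICC 0 to 0.10; 20, 50 or 100 preschools; blocks of 4.

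**Step 1: reproduce the stated sample size.** With pooled rate 0.57, n per arm = [1.96·√(2·0.57·0.43) + 0.842·√(0.25 + 0.2304)]² / 0.14² = 195.1, rounded up to 196. The total is 392, and 392/0.8 = 490, which agrees with about 500.

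**Step 2: closed-form approximation on the risk-difference scale.** SE = √((0.25 + 0.2304)/200) = 0.0490 and 0.14/0.0490 = 2.857. With perfect balance within preschools, the true variance is (1 − ICC) times the variance that the unadjusted model reports.

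- Factor by which the model SE is too large: 1/√(1 − ICC)
- Power with preschool accounted for: Φ(2.857/√(1 − ICC) − 1.96)
- Power without it: Φ((2.857 − 1.96)/√(1 − ICC))
- Actual size without it: 2·[1 − Φ(1.96/√(1 − ICC))]

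| ICC | SE too large by | Power with | Power without | Actual size |
|---|---|---|---|---|
| 0 | 0% | 0.815 | 0.815 | 0.050 |
| 0.05 | 2.6% | 0.834 | 0.821 | 0.044 |
| 0.10 | 5.4% | 0.853 | 0.828 | 0.039 |

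These figures are close to an upper bound for each ICC, because incomplete blocks and dropout break perfect balance. They also use a risk-difference variance and not the planned logistic model.

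**Step 3: simulation of the logistic analysis.** 400 analysed children, blocks of 4 within preschool, a random preschool effect on the logit scale, 2,500 runs per cell. The unadjusted logistic Wald test is compared with a preschool-stratified Cochran-Mantel-Haenszel test. The ICC is on the latent scale; latent 0.10 is about 0.08 on the observed scale of Step 2.

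| Preschools | Latent ICC | Type I error, unadjusted | Power, unadjusted | Power, stratified |
|---|---|---|---|---|
| 20 | 0.05 | 0.051 | 0.810 | 0.822 |
| 20 | 0.10 | 0.041 | 0.815 | 0.835 |
| 50 | 0.05 | 0.042 | 0.809 | 0.810 |
| 50 | 0.10 | 0.046 | 0.825 | 0.839 |
| 100 | 0.05 | 0.045 | 0.804 | 0.792 |
| 100 | 0.10 | 0.048 | 0.812 | 0.797 |

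Monte Carlo error is about 0.4 points on type I error and 0.8 points on power. Mean model SE divided by true SE was 0.98 to 1.03 for latent ICC up to 0.05 and 1.00 to 1.05 at 0.10. At latent ICC 0.20, outside the main range, type I error fell to 0.035 to 0.040 and the power difference was 1.8 to 3.6 points.

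With 100 preschools there are about 4 analysed children in each. This stratified test then loses strata that carry no information, and its power falls below that of the unadjusted test. That bears on the choice of method.

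**Step 4: random-intercept analysis.** A second simulation used 500 children, blocks of 4, 50 or 100 unequal preschools, 20% loss, a linear random-intercept model, observed-scale ICC and 4,000 runs per cell. The power gain was 0.1 to 0.4 points at ICC 0.01 to 0.02, about 1.1 points at 0.05 and about 2 points at 0.10. The unadjusted model's SE was 2 to 4% too large at ICC 0.05 to 0.10.

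**The case against.** The bracketed list names potential confounders. A factor balanced by design is not a confounder, so its absence does not show that the sponsor decided to ignore preschool. A condensed article may also leave the handling of strata to an analysis plan that is not shown here. This stands as a caution about intent. It does not remove the point: the article spells out both models and their covariates, and followed as written neither contains the one stratification factor that it names.

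The effect is small and rests on an assumed ICC. This stands. The adjusted model includes family socioeconomic level, and all trial children score at or above the 85th percentile for inhibition; both could lower the residual preschool ICC. Near zero there is nothing to gain.

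A reader might infer that the trial's p-values will be too conservative overall. The documents do not support that. Intervention parents are taught in groups of about 12 (Process - Intervention group), and clustering by group acts in the opposite direction. In a simulation with 100 preschools and an assumed group ICC of 0.02 to 0.05, the unadjusted test ran at 5.9 to 7.8% and a test with a preschool term alone at 6.2 to 8.4%. The conservatism described here belongs to the omission of preschool taken alone.

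A reader might also infer a biased effect estimate, an inflated type I error or a wrong sample size. None of these follows: balance within preschool protects the comparison, the omission by itself makes the test conservative, and the stated number reproduces.

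**Conclusion.** The point holds as a modest mismatch between design and analysis. Children are randomised within preschool and, as written, analysed as if they were not. The number of preschools and the ICC are unstated, so the size can only be bracketed. For ICCs from 0 to 0.10, the model-based standard error is about 0 to 5% too large and about 0 to 3 points of power are forgone. The upper ends come from the closed form with perfect balance; the random-intercept simulation gives about 2 points at ICC 0.10 and practically nothing at 0.01 to 0.02. It is worth correcting because the information is already collected for randomisation, not because the trial's conclusion is at risk.

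**What to change.** State in Data analyses that every primary logistic and linear model accounts for preschool, the stratification factor, by one method named in advance. Two methods suit, and they are not interchangeable for the binary outcome:

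- a random intercept for preschool, which gives a conditional odds ratio; or
- GEE grouped by preschool, if a marginal odds ratio is wanted.

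Do not use one dummy per preschool: with many small strata, a logistic model with that many dummies biases the odds ratio away from 1. Conditional logistic regression avoids that bias but discards strata in which all children share an outcome or an arm. The version called unadjusted can be kept by defining it as adjusted for preschool only.

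The cost is about one sentence, with no new data and no change in sample size. The downsides are slightly more complex models, a conditional odds ratio if the random intercept is chosen, and little or no gain if the preschool ICC is near zero. Clustering by parent group in the intervention arm needs its own provision; this change does not supply it.
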